## Abstract

**Background/Objectives**: The global burden of inflammatory bowel diseases (IBDs) continues to rise, with up to 50% of patients experiencing extraintestinal manifestations. Cardiovascular diseases (CVDs) are of particular concern, ranking as the second leading cause of mortality in this population. Despite a comparatively lower prevalence of traditional cardiovascular (CV) risk factors, the persistent inflammatory milieu and immune dysregulation inherent to IBD may contribute to heightened CVD risk. In this study, following a review of the current literature, an ongoing prospective trial designed to clarify CV risk profiles in IBD patients is detailed. **Methods**: A cohort of patients with IBD is being enrolled for comprehensive baseline evaluation of CV risk factors, lifestyle metrics, and disease characteristics. The incidence of major adverse cardiovascular events (MACEs) will be tracked and contrasted with a gender- and age-matched non-IBD cohort over a 2-year follow-up period. In cases of MACE occurrence, a multi-omics analysis—including genomic, proteomic, transcriptomic, and microbiome profiling—will be performed, along with a parallel evaluation in matched IBD controls without MACE. An artificial intelligence (AI) framework will support the analysis of this complex dataset. **Results**: To date, over 150 patients with IBD have been enrolled, and detailed phenotypic data and biological samples have been collected. **Conclusions**: We aim to introduce an IBD-specific correction factor for existing CV risk scores upon study completion. This is particularly relevant for individuals under 40 years of age, who are often inadequately assessed by current risk stratification models

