## 2. Materials and Methods

### 2.1. Study Population

Our first aim was to prospectively enroll a large cohort of IBD patients in the Unit of Gastroenterology of the Research Hospital San Donato Policlinic, San Donato Milanese (Mi), for 1 year to be compared with an age/gender-matched cohort under follow-up at the Unit of Cardiology of the same Institution. To this end, a set of specialized, privacy-preserving large language models (LLMs), coordinated by an agentic framework provided by Agora Labs [72], will be applied to different types of data sources containing records of patients under follow-up at the San Donato Policlinic to maximize enrollment. Specifically, the LLMs will extract clinical findings, diagnoses, disease activity indicators, family and social history items, past and current treatments, and other clinical data from all kinds of free-text notes. Under the clinicians’ supervision, such extracted data will drastically expand the underlying data pool and cohort size available for analysis. Data from both unstructured and structured sources will be harmonized to allow for multi-omics queries and model development, starting from descriptive statistics to the development of predictive algorithms. Following the signature of informed consent, all patients with confirmed IBD according with standard of care [3,4] will have a baseline evaluation of family and personal CVD risk factors with a standard questionnaire, including occurrence in family members of MACEs defined as ischemic heart disease (IHD), myocardial infarction (MI), stroke (ST), atrial fibrillation (AF), heart failure (HF), and thromboembolic events (TE). All patients will be evaluated with SCORE2 and the glyco-metabolic inflammatory axes. In case of the occurrence of a high CV risk score (>10 <20%), the carotid intima-media thickness (IMT) will be measured by Doppler ultrasound as a surrogate marker for subclinical atherosclerosis. In case of very high CV risk (more than 10% or more than 7.5% in subjects older than 69 years or younger than 50 years, respectively), the patient will be referred to the cardiologist (if not previously referred) for further investigations. To all patients, lifestyle modification measures will be given in written (i.e., stop smoking, minimize alcohol use, and follow a Mediterranean diet). Patients with IBD will undergo a careful baseline evaluation of disease activity and ongoing therapy, standard laboratory investigations, ileocolonoscopy, and biopsies as standard of care [3,4]. In addition, in all IBD patients, different biological materials (whole blood, plasma/serum, tissues, and stool samples) will be collected and stored in the Policlinic Biobank. All patients will then be followed for at least 2 years, and every year, a re-evaluation of IBD activity, ongoing therapy, lab tests, and monitoring of the occurrence of MACEs will be recorded. The enrollment of the study population will be performed according to the protocol approved by the local ethics committee (Milan 29/1/2025 CET 510-2024), which was recently also registered as NCT07095634.

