### 2.3. Prospective Evaluation

At the end of the 2-year follow-up, all patients in the IBD cohorts and the control population will be re-evaluated in terms of CVD risk using SCORE 2, the standard laboratory and cardiologic investigations will be repeated, and the occurrence of new MACEs will be reported. All patients with IBD will be regularly evaluated during the follow-up at 3–6 month intervals, and all will receive a clinical, endoscopic, and histologic evaluation at the end of follow-up. The subgroup of patients with the occurrence of MACEs and those with clinical and endoscopic remission will also repeat the transcriptomics and metagenomics evaluation.

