### 2.4. Objectives of the Study

The primary objective of the study will be to evaluate the basal CVD risk in our IBD population compared with the age- and gender-matched cohort of non-IBD patients.

The secondary objectives will be as follows:–Correlation of the basal CVD risk with multi-omics biomarkers, disease activity, lifestyle (i.e., diet, smoking) and therapy;–To evaluate the occurrence of MACEs at the end of follow-up in the patients with IBD and control populations;–To investigate the possible correlation between high CVD risk and MACE occurrence with multi-omics findings;–To identify possible biomarkers of increased CVD risk compared with the control population;–To establish possible correction factors to apply to the standard traditional CVD risk score to incorporate the IBD inflammatory burden.

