The power of our sample was estimated by Cohen’s h effect size for proportions based on different hypotheses about the annual incidence rate of main MACEs in Italy (ISTAT—National Institute of Statistics), a range from 1% to 5% per year, and the estimated increase in cardiovascular events in the Crohn’s disease and ulcerative colitis groups, a range from 1.25 (25% increase) to 3.5 (250% increase). Under the assumption of an incidence rate of 1% per year in the control population, a sample size of 300 patients with IBD (CD and UC) and 300 matched controls will have 80% power to detect an HR of 2.5 or greater. Under the assumption of an incidence rate of 5% per year, there will be approximately 80% power to detect a hazard ratio equal to 1.6. The recruitment period was set to 1 year with 4 years of follow-up (2 years retrospective and 2 years prospective) for a total duration of 5 years. The significance level was set at 5%. A dropout of 5% in both groups is assumed. Effect size parameters: Follow-up period of 3 years retrospectively and 2 years prospectively; alpha (α) of 0.05 (standard significance level); power (1—β) of 90%.

For genomics, logistic regression and generalized linear models will be used for association analyses between the identified genetic variants and clinical outcomes, adjusting for confounders, such as age, sex, and disease duration.

Transcriptome data will be analyzed for differential expression patterns, with statistical significance assessed through empirical Bayes methods, followed by pathway enrichment analysis using gene set enrichment analysis (GSEA) and functional network mapping through tools such as STRING (consortium 2024) or Cytoscape (ver. 3.10.3).

Microbiome data will undergo community profiling through alpha and beta diversity metrics, and associations with clinical endpoints will be tested via multivariate analysis methods, such as canonical correspondence analysis (CCA) and redundancy analysis (RDA). Furthermore, metagenomic functional profiles will be reconstructed using PICRUSt2 or HUMAnN3, allowing for functional comparison across patient subgroups. Integration across omics layers will be realized through data integration analysis for biomarker discovery using latent components (DIABLO) and complemented by machine learning-driven feature selection techniques (e.g., LASSO, elastic-net).

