Targeted proteomics will be analyzed by ANOVA and Tukey’s for a multiple comparison test. To evaluate the concordance of histological evaluation (active/remission) of different scoring system and Claudin 2 immunostaining, Cohen’s kappa (k) will be evaluated.

In addition, to carry out the systematic evaluation of the large, multidimensional dataset, overcoming the limitation of sample size and length of follow-up, and to detect unexpected pathogenetic hypotheses and biomarkers, an artificial intelligence model will be implemented [78]. This will be performed with the use of the Agora Labs platform. Agora^®^ Node supports the training of machine-learning and AI algorithms in a localized or federated architecture, thus allowing multivariate analysis to correlate clinical and multi-omics findings and other attributes included in the study, as well as deeper evaluation of multidimensional datasets by applying random forest (RF) and support vector machine (SVM) models, among others. Random forest (RF) and support vector machine (SVM) models, specifically, will be tested on feature selection tasks and on the identification of predictors of cardiovascular events from clinical and multi-omics data. RF will highlight influential factors (e.g., genetic markers, microbiome composition, and inflammatory markers), which will then be prioritized in subsequent modeling stages. SVMs, known for their performance with smaller datasets, will then refine classification based on selected features, creating a baseline model for cardiovascular risk. Neural networks, particularly deep neural networks (DNNs) or convolutional neural networks (CNNs), will also be tested in the handling of the study’s complex, high-dimensional dataset, especially in identifying non-linear relationships across genomics, transcriptomics, and proteomics data. After RF and SVM have highlighted the most predictive features, these will be integrated into neural networks to improve accuracy in predicting cardiovascular events.

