In Italy, there are currently an estimated 250,000 to 300,000 patients with IBD, with projections indicating a possible doubling over the next decade [1]. This trend will inevitably place greater pressure on the national healthcare system. A major strength of our study is its structured approach—applying standard care protocols and monitoring both clinical disease features and lifestyle data over a 5-year period (3 years retrospectively, 2 years prospectively). In addition, we will compare this cohort to a well-matched, rigorously followed control population. Multi-omics analysis will be used to identify potential biomarkers associated with increased cardiovascular risk.

Upon completion of the study, we aim to propose an IBD-specific correction factor to enhance the accuracy of existing CV risk scoring systems. This will be particularly valuable for younger patients—especially those under 40 years—who are not adequately captured by current tools.

Indeed, this subgroup appears to show a more pronounced disparity in MACE incidence compared to the general population. Notably, this will be the first prospective investigation in Italy specifically designed to evaluate CVD risk in patients with IBD and one of only a few worldwide [43]. The findings of this study will offer important insights to clinicians, researchers, and policymakers, contributing to more informed strategies to reduce cardiovascular morbidity and mortality in this vulnerable group.

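### The MACE window is contradictory, and the version behind the power figures would place some IBD events before the SCORE2 and samples meant to predict them

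*Protocol article*

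**What the plan says.** The article gives three accounts of the period over which MACEs count.

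- **Two prospective years.** In the Abstract, MACE incidence is "contrasted with a gender- and age-matched non-IBD cohort over a 2-year follow-up period". In Section 2.3, at the end of the 2-year follow-up, "the occurrence of new MACEs will be reported".
- **Two plus two years.** The power paragraph of Section 2.5 has "4 years of follow-up (2 years retrospective and 2 years prospective", which with 1 year of recruitment gives its total duration of 5 years.
- **Three plus two years.** The same paragraph lists among its effect-size parameters: "Follow-up period of 3 years retrospectively and 2 years prospectively". The Discussion repeats this split, "over a 5-year period (3 years retrospectively, 2 years prospectively", when describing the monitoring of disease features and lifestyle.

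The measurements begin at enrolment. Section 2.1 has consent first, then SCORE2 and the baseline work-up, and "in all IBD patients, different biological materials (whole blood, plasma/serum, tissues, and stool samples) will be collected and stored in the Policlinic Biobank". Sections 2.2 and 2.3 add later repeats (stool, plasma, SCORE2, and transcriptomics in some patients). No sample is described as taken before enrolment.

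The measurements are then to be related to MACEs. Section 2.4 lists "To investigate the possible correlation between high CVD risk and MACE occurrence with multi-omics findings" and a correction factor for the standard risk score. Section 2.5 plans machine-learning models for "the identification of predictors of cardiovascular events from clinical and multi-omics data". The logistic model in Section 2.5 takes MACE as yes or no over the study period, without saying which window that is.

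**The concern.** A predictor has to be measured before the event it predicts. If a patient's infarction fell in the 2 or 3 years before enrolment, that patient's baseline plasma, stool, tissue, lipids and blood pressure are all post-event. They can reflect the event itself and any change in treatment or lifestyle after it. Entered as predictors, they would invite reverse causation. Likewise, a SCORE2 value obtained after an event cannot show how well SCORE2 predicted it.

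Such patients can enter the cohort. Section 2.1 takes all patients with confirmed IBD and the Conclusions speak of consecutive patients. Only the controls are described as free of known cardiovascular disease at baseline.

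At stake are the within-IBD biomarker findings and the correction factor, both presented as main products of the study. Germline SNPs are not affected by the timing, because genotype does not change.

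**Working it through.** **Step 1. Which window do the power figures use?**

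Inputs from Section 2.5: 300 IBD patients and 300 controls; alpha 5% (taken as two-sided, since sidedness is not stated); Cohen's h; control rate 1% per year with HR 2.5, or 5% per year with HR 1.6; stated power 80% and approximately 80%.

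Formulas, for annual rate r and T years:
- p0 = 1 − exp(−rT) and p1 = 1 − exp(−r·HR·T)
- h = 2·arcsin(√p1) − 2·arcsin(√p0)
- power = Φ(h·√(300/2) − 1.96)

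| Scenario | T (years) | p0 | p1 | h | Power |
|---|---|---|---|---|---|
| 1%/y, HR 2.5 | 4 | 0.0392 | 0.0952 | 0.229 | 79.9% |
| 1%/y, HR 2.5 | 2 | 0.0198 | 0.0488 | 0.163 | 51.4% |
| 5%/y, HR 1.6 | 4 | 0.1813 | 0.2739 | 0.222 | 77.6% |
| 5%/y, HR 1.6 | 2 | 0.0952 | 0.1479 | 0.162 | 51.0% |

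The 4-year rows reproduce the plan's figures. Using simple proportional risk (rate × years) instead, 2 years gives 53.5% and 59.4%, still well short of 80%. The power statement therefore counts retrospective MACEs as outcome events.

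**Step 2. What share of IBD events would precede the enrolment measurements under that window?**

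At a constant rate, share = retrospective years / total years:
- 2+2: 2/4 = 50%
- 3+2: 3/5 = 60%

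**Step 3. Event counts in 300 IBD patients at 1% × 2.5 = 2.5% per year.**

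Simple counts:
- before enrolment: 300 × 0.025 × 2 = 15, or 300 × 0.025 × 3 = 22.5
- after enrolment: 300 × 0.025 × 2 = 15

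First events only, 300 × (1 − exp(−0.025·T)):
- 2 years: 14.6
- 3 years: 21.7
- 4 years: 28.5
- 5 years: 35.3

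The first-event shares before enrolment are 14.6/28.5 = 51% (2+2) and 21.7/35.3 = 61% (3+2), close to Step 2.

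**Step 4. What the constant-rate figure leaves out.** A patient whose MACE was fatal before enrolment cannot be enrolled. The observed retrospective share would be lower than Step 2 suggests, and the retrospective cases would all be survivors. The documents give no case fatality, so the reduction cannot be sized.

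**The case against.** A reader might infer that half or more of the MACEs in the biomarker models do precede their predictors. The documents do not support that.

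- The Abstract, Sections 2.1 and 2.3 and the Conclusions all describe MACEs recorded during follow-up after the baseline visit. On that account the timing problem from retrospective events disappears.
- No passage says that retrospective MACEs enter the omics, machine-learning or correction-factor analyses.
- The power calculation concerns IBD against controls. It shows how that comparison was sized, not which events feed the within-IBD models.
- The five years in the Discussion refer to disease features and lifestyle data, not to MACEs.

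A reader might also infer that the correction factor would be inflated because treated post-event patients score low. The article gives no method for deriving the factor, so neither the direction nor the size of any bias can be shown.

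The repeat samples could serve a legitimate analysis of change, and the article does not call them predictors. Which sample and which events enter each model may also be settled in an analysis plan that is not shown.

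These points limit the concern but do not remove it. The article itself states three incompatible windows, and its power holds only under a longer one. The yes/no MACE outcome is tied to a study period whose stated 5-year total includes retrospective time. That is a contradiction in the text, not an omitted detail.

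**Conclusion.** The concern holds in conditional form. The outcome window is contradictory, and the 80% power depends on about 4 years of events, against about 51% with 2 (Cohen's h, exponential risk, two-sided 5%). If the Section 2.5 window also governs the prediction and correction-factor work, roughly 50% or 60% of IBD MACEs would come before the SCORE2 and non-germline measurements used to predict them. That range assumes a constant event rate and overstates the observed share to the extent that earlier events were fatal. If only prospective MACEs count, the time order of predictor and event is sound, but the stated power is not. Either way, the text needs correcting before analysis.

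**What to change.** 1. Reconcile the Abstract, Sections 2.3 and 2.5 and the Discussion on one MACE window for each analysis.
2. State that every MACE prediction analysis using SCORE2 or non-germline omics, and the SCORE2 correction factor, counts only first MACEs after the enrolment sample and score, with only enrolment measurements as predictors.
3. Record retrospective MACEs as a prior-MACE baseline covariate, or describe them separately.
4. Analyse samples taken after a MACE as change, not as predictors.
5. If the IBD-versus-control MACE comparison is also limited to prospective events, restate its power as about 51% for the two stated scenarios.

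The cost is wording, plus fewer countable events: about 15 rather than about 28 to 35 IBD first events at 1% per year and HR 2.5. The events given up come before the measurements, so they could not have supported a claim of prediction.

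### The sizing paragraph gives two unreconciled bases for 300 per group, 80% power with 2+2 years and 90% power with 3+2 years, and the method that reproduces the 80% does not give 90% at the stated hazard ratios

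*Protocol article*

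**What the plan says.** All the sizing figures are in section 2.5 (Statistical Analysis) of the Protocol article. The power was estimated with Cohen's h for proportions, with control event rates over "a range from 1% to 5% per year".

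- **First basis.** At a 1% annual control rate, 300 patients with IBD and "300 matched controls will have 80% power to detect an HR of 2.5 or greater". At 5% a year, "there will be approximately 80% power to detect a hazard ratio equal to 1.6". The follow-up that goes with these is "4 years of follow-up (2 years retrospective and 2 years prospective"), and 5% dropout is assumed in each group.
- **Second basis.** The paragraph's closing list of effect-size parameters reads "Follow-up period of 3 years retrospectively and 2 years prospectively; alpha (α) of 0.05 (standard significance level); power (1—β) of 90" per cent. No hazard ratio, event rate or number of patients is attached to it.

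The Discussion (section 4) repeats the second follow-up period, three retrospective plus two prospective years. Section 2.4 makes MACE occurrence a secondary objective; the primary objective is baseline CVD risk.

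**The concern.** One paragraph gives the reader two powers and two exposure periods, and only one sample size. Nothing says which pair governs. The repetition of 3+2 years in the Discussion makes it hard to treat the closing line as an isolated slip.

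This paragraph is the only rationale shown for 300 per group. If the 90% is quoted for the between-cohort MACE comparison at the hazard ratios the paragraph names, a null result would be read as stronger evidence against an excess than the calculation behind the 80% supports.

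**Working it through.** **Inputs, all from section 2.5.** n = 300 per group; control rate r = 1% a year with HR 2.5, and r = 5% a year with HR 1.6; follow-up T = 4 years (2+2) or 5 years (3+2); significance level 5%; dropout 5%. Sidedness is not stated, so two-sided is assumed. Full follow-up of every evaluable subject is also assumed.

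**Formulas.**

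- Constant hazard: p1 = 1 − exp(−rT), p2 = 1 − exp(−r·HR·T).
- Annual compounding: p1 = 1 − (1 − r)^T, p2 = 1 − (1 − r·HR)^T.
- Cohen's h = 2·asin(√p2) − 2·asin(√p1).
- Power = Φ(h·√(n/2) − 1.96).

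**Step 1: the plan's 80% figures, at 4 years with constant hazard.**

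- HR 2.5 at 1%: p1 = 1 − exp(−0.04) = 0.0392; p2 = 1 − exp(−0.10) = 0.0952; h = 0.2285; h·√150 = 2.799; power = Φ(0.839) = 79.9%.
- HR 1.6 at 5%: p1 = 1 − exp(−0.20) = 0.1813; p2 = 1 − exp(−0.32) = 0.2739; h = 0.2219; h·√150 = 2.717; power = Φ(0.757) = 77.6%.

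Both agree with the printed 80% and approximately 80%. Annual compounding gives 80.9% and 81.3%.

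**Step 2: the same method at 5 years.**

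- HR 2.5 at 1%: p1 = 0.0488; p2 = 0.1175; h = 0.2544; power = Φ(3.116 − 1.96) = 87.6%.
- HR 1.6 at 5%: p1 = 0.2212; p2 = 0.3297; h = 0.2439; power = Φ(2.987 − 1.96) = 84.8%.

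| 300 per group | 4 years | 5 years |
|---|---|---|
| HR 2.5 at 1%, constant hazard | 79.9% | 87.6% |
| HR 2.5 at 1%, compounding | 80.9% | 88.4% |
| HR 1.6 at 5%, constant hazard | 77.6% | 84.8% |
| HR 1.6 at 5%, compounding | 81.3% | 87.9% |

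The shortfall against 90% is 8.7 to 12.4 points at 4 years and 1.6 to 5.2 points at 5 years.

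**Step 3: the stated dropout.** 300 × 0.95 = 285 evaluable per group. With constant hazard, power for HR 2.5 and HR 1.6 is 77.9% and 75.4% at 4 years, and 85.9% and 82.9% at 5 years.

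**Step 4: can 90% be obtained another way?** It can, for one scenario at a time.

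- Risk as rate × years, 5 years, HR 2.5 (5.0% v 12.5%): 91.4% with 300, 90.0% with 285.
- Schoenfeld log-rank, 5 years, HR 2.5: events = 300 × (0.0488 + 0.1175) = 49.9; power = Φ(√(49.9/4)·ln 2.5 − 1.96) = 89.9%.
- Rate × years, 4 years, HR 1.6 (20% v 32%): 92.1% with 300, 90.8% with 285.
- One-sided test, rate × years, 4 years, HR 2.5: 90.4%.

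Rate × years does not explain the paragraph as a whole. It gives 92.1% at 4 years and 97.7% at 5 years for HR 1.6, where the plan prints about 80%.

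**Step 5: what 90% would mean with 300 evaluable over 4 years.** Solving the constant-hazard formula for the hazard ratio gives about 2.8 at 1% a year and about 1.7 (1.735) at 5% a year.

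**The case against.** The best defence is that the 90% line names no sample size, hazard ratio or rate, so it may be a leftover planning input and not a claim about 300 per group. Power is also a function of the effect: 300 evaluable subjects over four years have 80% power at HR 2.5 and 90% at about HR 2.8, and both values lie inside the plan's range of 1.25 to 3.5. On power alone, the two numbers can therefore coexist. That stands, and it limits what can be said about the 90%. It does not help the follow-up periods: 2+2 and 3+2 cannot both describe the exposure. Nor does it tell the reader what effect the 90% refers to.

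A reader might go further and infer that the 90% can only come from a five-year rate × years calculation. The supporting coincidence is that this route needs 285 per group, and 285/0.95 = 300. The documents do not support that inference. A five-year Schoenfeld calculation and a four-year rate × years calculation also land near 90%, and the five-year shortcut gives 97.7% in the other scenario. The origin of the 90% is unknown.

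It is also fair to say that the body of the paragraph states 80% twice with its assumptions attached, and that MACE occurrence is a secondary objective.

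**Conclusion.** The point holds as an unreconciled contradiction in the sizing paragraph. The 80% statements belong to four years of follow-up. The two conversions that reproduce both of them give 90% at neither four nor five years for HR 2.5 at 1% or HR 1.6 at 5%: they are about 9–12 points short at four years and about 2–5 points short at five.

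A flat statement that power is overstated by about 10 points would not be supported. That size requires pairing the 90% with those hazard ratios, with four years, and with constant-hazard or compounded risks. With rate × years at four years the gap is about 6 points for HR 2.5 (90 − 83.9) and reverses to about −2 for HR 1.6 (90 − 92.1).

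The result rests on a two-sided 5% test, constant rates and complete follow-up of the evaluable subjects. It calls for correcting a stated figure for a secondary comparison and does not threaten the primary objective.

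**What to change.** 1. Keep one follow-up period and use it in both section 2.5 and the Discussion. It should be the exposure actually analysed for MACE in both cohorts.
2. Delete the closing 90% line, or restate it with the hazard ratio, control rate and number of patients it refers to.
3. Report one power per scenario, giving the hazard ratio, control rate, evaluable number after dropout, sidedness and the conversion 1 − exp(−rate × t).

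For 285 evaluable per group, the sentence for HR 2.5 at 1% a year and HR 1.6 at 5% a year would give about 78% and 75% if four years is kept, or about 86% and 83% if five years is kept. Any other exposure needs its own calculation. If a 90% figure is wanted for 300 evaluable subjects over four years, it applies to hazard ratios of about 2.8 and 1.7 respectively.

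The cost is rewording. No extra patients or data are needed, but the stated power becomes less favourable.

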### 2.2. Multi-Omics Evaluation

The second aim is to undertake an extensive multi-omics, metabolic, and histological evaluation.

Genomics: Germline genetic markers using DNA extracted from peripheral blood samples collected from patients with IBD will be evaluated. A panel of approximately 30 single-nucleotide polymorphisms (SNPs) will be analyzed using TaqMan allelic discrimination assays [73]. The list of SNPs to be evaluated will be selected by reviewing the available literature of genes involved in immune and inflammatory processes. Univariate and multivariate stepwise logistic regression models will be used to identify the variables associated with CVD risk and MACEs in patients with IBD.

Transcriptomics: Genome-wide expression profiling of mRNA will be conducted using RNAs extracted from tissue samples collected before and after treatment of selected patients to identify pivotal and critical genes associated with therapy response. The designed whole-transcript array used will provide the most accurate, sensitive, and comprehensive measurement of protein coding and long intergenic non-coding RNA transcripts [74]. Gene expression microarray analysis and functional enrichment analysis of the sample data will be performed to reveal abnormally expressed genes at the tissue level and to elucidate the biological significance of the differential expression pattern.

Metagenomics: A comprehensive sequencing of the gut microbiome will be performed. DNA will be extracted from stool samples at baseline and after 2 years of follow-up, and the variable V3 and V4 regions of the 16S rRNA gene will be sequenced. All procedures will follow extensively validated protocols to perform accurate taxonomic and functional profiling of the microbiome composition using newly developed custom bioinformatics and statistical tools [75].

Proteomics: To perform proteomic profiling of plasma samples at baseline and at the end of follow-up, cutting-edge technology will be applied to overcome the limitation of the outstanding dynamic range of plasma proteins [76]. With these targeted proteomic approaches, we will analyze the potential modulation of proteins involved in the most relevant physio-pathological pathways, including inflammation, immune response, and metabolic dysregulation.

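### Stepwise regression for MACEs is a poor stated choice at the expected event counts, and AI cannot overcome few events or short follow-up

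*Protocol article*

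**What the plan says.** Section 2.2 (Genomics) names the method: "Univariate and multivariate stepwise logistic regression models will be used to identify the variables associated with CVD risk and MACEs in patients with IBD". The candidates include a literature-based panel of about 30 SNPs. For genomics, Section 2.5 also plans logistic and generalised linear models adjusted for age, sex and disease duration. It lists LASSO and elastic-net among the feature-selection tools for integrating the omics layers.

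Section 2.5 then describes the AI work. A random forest ranks influential factors, an SVM refines classification on the selected ones, and finally "After RF and SVM have highlighted the most predictive features, these will be integrated into neural networks to improve accuracy in predicting cardiovascular events". One stated purpose of the AI model is "overcoming the limitation of sample size and length of follow-up".

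The power statement in the same section rests on "a sample size of 300 patients with IBD (CD and UC) and 300 matched controls" and two scenarios:

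- "Under the assumption of an incidence rate of 1% per year in the control population": "80% power to detect an HR of 2.5 or greater".
- "Under the assumption of an incidence rate of 5% per year": "approximately 80% power to detect a hazard ratio equal to 1.6".

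The article gives no expected number of MACEs and does not say how the prediction models will be evaluated.

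**The concern.** Two things are wrong in the text itself. Stepwise selection is a weak method when the outcome is rare and the candidates are many: the chosen set changes with small changes in the data, and the p-values of the final model ignore the search that produced it. And the claim that AI overcomes limited sample size and follow-up is untrue, because a classifier uses the events that occurred and cannot create more.

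A third risk is conditional. A chain in which one model picks features for the next gives misleading accuracy if the picking is done once on all patients and only the last model is cross-validated.

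At stake are secondary objectives (Section 2.4): biomarkers of raised risk, and correction factors for the standard risk score. The Abstract and Discussion present the correction factor as the main product, especially for patients under 40.

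**Working it through.** **Inputs (Section 2.5).** 300 IBD patients and 300 controls; control rate 1% to 5% per year; ratio 1.25 to 3.5; power scenarios 1% with HR 2.5 and 5% with HR 1.6; 5% dropout; 2 prospective years, plus 2 retrospective years in one sentence and 3 in another. About 30 SNPs (Section 2.2).

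**Step 1. Reproduce the stated power.** With cumulative risk p = 1 − exp(−rate × HR × T), h = 2·arcsin√p₂ − 2·arcsin√p₁, and power = Φ(h·√(n/2) − 1.96), for n = 300, T = 4 years and a two-sided 5% test (sidedness is assumed):

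- 1%, HR 2.5: p₁ = 1 − exp(−0.04) = 0.0392; p₂ = 1 − exp(−0.10) = 0.0952; h = 0.2285; power = Φ(2.799 − 1.96) = 79.9% (stated 80%).
- 5%, HR 1.6: p₁ = 1 − exp(−0.20) = 0.1813; p₂ = 1 − exp(−0.32) = 0.2739; h = 0.2219; power = Φ(2.717 − 1.96) = 77.6%, or 78.4% by Schoenfeld's formula (stated as approximately 80%).

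So the stated power draws on four years of events. With 2 years alone, the same formula gives about 51% in both scenarios.

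**Step 2. Expected IBD MACEs over the 2 prospective years.** Events = 300 × (1 − exp(−rate × HR × 2)):

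- 1%, HR 2.5: 300 × (1 − exp(−0.05)) = 14.6 (13.9 with 285 after dropout)
- 5%, HR 1.6: 300 × (1 − exp(−0.16)) = 44.4 (42.1 with 285)
- Lowest, 1% and 1.25: 300 × (1 − exp(−0.025)) = 7.4
- Highest, 5% and 3.5: 300 × (1 − exp(−0.35)) = 88.6

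**Step 3. Events per SNP.** 14.6/30 = 0.5 and 44.4/30 = 1.5, before any other covariate or omics layer. Germline genotype does not change, so SNP models could also use retrospective events, with survival to enrolment as a caveat. Over four years, 300 × (1 − exp(−0.10)) = 28.5 and 300 × (1 − exp(−0.32)) = 82.2, or 0.95 and 2.7 per SNP. Plasma, stool and tissue taken from enrolment onward cannot predict events that came before.

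**Step 4. Chance findings among the SNPs.** If 30 independent null SNPs were each tested at an uncorrected 5%, the expected number of false positives is 30 × 0.05 = 1.5, and the chance of at least one is 1 − 0.95³⁰ = 79%. The article sets no per-SNP threshold, so this is an illustration.

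**Step 5. What selection before evaluation would do.** Simulation with 300 patients and noise features only (true AUC 0.50). Feature counts, number of features kept and network size are assumptions. The filter with a linear classifier used 60 replicates, the full chain only 6. The 48 events are the linear count 300 × 0.05 × 1.6 × 2.

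| Method | Events | Features | AUC, selection on all data then cross-validation | AUC, selection inside folds |
|---|---|---|---|---|
| Filter + linear | 15 | 30 | 0.70 | 0.50 |
| Filter + linear | 15 | 200 | 0.87 | 0.52 |
| Filter + linear | 15 | 1000 | 0.94 | 0.49 |
| Filter + linear | 48 | 30 | 0.63 | 0.51 |
| Filter + linear | 48 | 200 | 0.75 | 0.50 |
| Filter + linear | 48 | 1000 | 0.81 | 0.50 |
| RF, SVM, neural network | 15 | 500 | 0.89 | 0.52 |
| RF, SVM, neural network | 48 | 500 | 0.78 | 0.54 |

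The inflation shrinks with more events but does not vanish at 48.

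**The case against.** A reader might infer that the plan picks and tests features on the same data and so will report strong predictors from noise. The documents do not support that. Section 2.5 gives an order of methods and no evaluation scheme; the same order is valid if repeated inside each fold. An article may leave fold structure, tuning and calibration to the full protocol or SAP. The simulated AUCs therefore show the cost of one possible reading, not what this study will report. That objection stands.

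It is also fair that about 15 events is one scenario among many, that SNP models may draw on retrospective events, that the stepwise models also cover CVD risk (where MACE counts are not the limit), and that multiplicity across SNPs is ordinary SAP content. LASSO and elastic-net are already named. The primary objective, baseline CVD risk against controls, is untouched, and the AI work is worded as testing methods and detecting unexpected hypotheses. No sentence ties the correction factor to the neural-network chain. Confining neural models to continuous outcomes would be a matter of preference.

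None of this rescues stepwise selection for MACEs or the claim about sample size and follow-up. Both are written in the article, and no further document could make the claim true.

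**Conclusion.** The point holds in two firm parts and one conditional part.

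- **Firm:** stepwise logistic regression is a poor stated method for MACEs at 0.5 to 1.5 events per SNP in the two power scenarios, or about 1 to 2.7 with four years of events.
- **Firm:** the statement that AI overcomes limited sample size and follow-up is wrong.
- **Conditional:** if the selection chain is completed on all data before evaluation, accuracy figures would be badly inflated; if it is nested, they would not.

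The event counts assume 300 patients, exponential risk and the article's own rates and ratios. The firm parts do not depend on which scenario is true. This should be corrected, but it does not threaten the primary objective.

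**What to change.** 1. In Section 2.2, replace stepwise selection for MACEs with penalised regression (Firth, ridge, LASSO or elastic-net), with false-discovery control, such as Benjamini–Hochberg, across the SNP panel.
2. In Section 2.5, or in the SAP with a sentence here, state that every random-forest, SVM and LASSO selection step and all tuning are repeated inside the resampling folds. Report only outer-fold discrimination and calibration, set against SCORE2 alone.
3. Label MACE prediction exploratory, and give the expected number of events with its range.
4. Delete the claim that AI overcomes the limits of sample size and follow-up. It is enough to say that the methods explore high-dimensional data for hypotheses.

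The cost is wording and some computing time. Section 3.1 places the multi-omics analysis in the last 3–6 months of the project, so there is time. The downside is lower, but honest, reported accuracy.
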